### Sample size calculation

2.4

This study is an exploratory investigation, with the primary outcome measure defined as the reduction in the monthly migraine days (MMD) from baseline after 4 weeks of treatment. As a novel acupuncture technique, Fu’s Subcutaneous Needling (FSN) inevitably lacks high-quality randomized controlled trials (RCTs) to inform sample size estimation. Therefore, reference is made to an internationally rigorous RCT on acupuncture for migraine without aura (23), and the sample size is estimated based on this study, combined with clinical FSN practice and the current study design. The hypothesis posited comparable effect sizes between the two interventions (FSN group and flunarizine hydrochloride group) in this trial and those observed in the prior study’s acupuncture and flunarizine hydrochloride groups. The referenced study reported that after 4 weeks of treatment, the MMD in the acupuncture group decreased by 4.1 ± 3.5 from baseline, while the MMD in the flunarizine hydrochloride group decreased by 1.9 ± 2.3 from baseline. To verify whether the efficacy of FSN is at least not inferior to that of flunarizine hydrochloride, a non-inferiority test is employed. Based on previous research (24), the most commonly selected non-inferiority margin for Monthly Migraine Days (MMD) in migraine studies is 1. The calculation is performed using the Non-Inferiority Tests for the Difference Between Two Means in PASS 15.0 software. With *α* = 0.05 (two-sided), power (1−*β*) = 0.9, and an anticipated 25%dropout rate, a total of 44 participants (22 per group, 1:1 ratio) are required to detect a statistically significant difference in MMD changes between the two groups.

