**Figure 4 fig4:**
[figure not shown]
Placement of NIRS.

**Table 1 tab1:** Study schedule.

Stage	Baseline	Treatment			Follow-up (after treatment)		
Time point	Day 0	Day 1	→	Day 28	Day 28	→	Day 168
Enrolment							
Eligibility	×						
Informed consent	×						
Allocation	×						
Interventions							
FSN		×					
Flunarizine hydrochloride		×					
Assessment							
MMD	×			×	×	×	×
MSQOL scores	×			×	×	×	×
VAS scores	×			×	×	×	×
MIDAS scores	×			×	×	×	×
Headache diaries	×			×	×	×	×
NIRS		4 measurements					
Adverse events	×	×					

Fu’s Subcutaneous Needling (FSN), developed by [name], is a novel acupuncture technique derived from traditional Chinese medicine and grounded in anatomy, physiology, and myofascial trigger point theory. It involves repetitive sweeping of the subcutaneous loose connective tissue over pathologically tense muscles to reduce peripheral muscle tension (19), combined with resistance exercises to promote tissue reperfusion. This approach rapidly alleviates muscle ischemia and hypoxia (20), reduces mechanical compression on surrounding tissues, and demonstrates notable efficacy in pain management (21, 22).

Currently, there is a paucity of clinical studies on the application of floating acupuncture for MWoA, and objective assessments of its therapeutic effects are lacking. Therefore, we propose a randomized controlled trial to assess the clinical efficacy and underlying mechanisms of FSN in treating MWoA, with the goal of identifying safer and more effective treatment strategies. We hypothesize that floating acupuncture is non-inferior to flunarizine hydrochloride in alleviating pain intensity, reducing attack frequency, and enhancing quality of life in MWoA patients.

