## Conclusion

8

The hypothesis of this study is that FSN therapy is not inferior to flunarizine hydrochloride in improving headache intensity and attack frequency in patients with migraine without aura, and that its therapeutic effects may be sustained over time. The study aims to test this hypothesis in a controlled clinical trial. The results may demonstrate the clinical utility of FSN therapy for migraine without aura and facilitate its wider implementation.

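### The 90% power stated for the non-inferiority test depends on a borrowed 2.2-day advantage for FSN and, at the stated two-sided alpha of 0.05, is not reached even with that advantage (84%; 15% at equal efficacy)

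*Protocol article*

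**What the plan says.** The question is one of non-inferiority throughout the protocol article. The Introduction states: "We hypothesize that floating acupuncture is non-inferior to flunarizine hydrochloride". Section 2.4 (Sample size calculation) says: "To verify whether the efficacy of FSN is at least not inferior to that of flunarizine hydrochloride, a non-inferiority test is employed". Section 8 (Conclusion) gives the hypothesis as "FSN therapy is not inferior to flunarizine hydrochloride in improving headache intensity and attack frequency".

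Section 2.4 explains that FSN has no good randomised evidence to draw on. It therefore takes an acupuncture trial in migraine without aura as its reference and supposes effects in this trial comparable to "those observed in the prior study’s acupuncture and flunarizine hydrochloride groups". In that trial, "the MMD in the acupuncture group decreased by 4.1 ± 3.5 from baseline, while the MMD in the flunarizine hydrochloride group decreased by 1.9 ± 2.3". The remaining inputs are a margin of 1 day, alpha 0.05 described as two-sided, power 0.9, 25% dropout and a PASS routine for non-inferiority of two means. The result is 22 per group, 44 in total. No power is given for any other true difference.

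Section 6 (Statistical analysis) plans two-sided tests at p < 0.05 for the between-group difference in MMD change.

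**The concern.** The two assumed reductions differ by 4.1 − 1.9 = 2.2 days in favour of FSN, more than twice the margin. The calculation therefore has 2.2 + 1 = 3.2 days of room before the non-inferiority limit. If the two treatments were equally effective it would have 1 day. The 4.1 days belongs to a different needling technique, and section 2.4 itself says FSN trial data are lacking. The stated 90% therefore rests on the least certain input in the plan.

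The stated alpha is a second difficulty. A two-sided 0.05 corresponds to one-sided 0.025 for a non-inferiority test, and 22 per group needs to be checked at that level.

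What is at stake is how the result is read. If FSN is about as good as flunarizine, or only modestly better, the trial will often fail to exclude the margin. A reader who relies on 90% power could take that failure as evidence against FSN, when it is largely what a trial of this size would produce.

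**Working it through.** **Inputs, all from section 2.4:** reductions 4.1 (SD 3.5) and 1.9 (SD 2.3); margin 1 day; 22 per group; 25% dropout; alpha 0.05 described as two-sided; power 0.9.

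**Common quantities**
- Root-mean-square SD = √[(3.5² + 2.3²)/2] = √[(12.25 + 5.29)/2] = 2.96.
- Evaluable per group = 22 × 0.75 = 16.5, taken as 16.
- Standard error of the difference = 2.96 × √(2/16) = 1.047.
- For a true FSN advantage d, the noncentrality is (d + 1)/1.047 with 2 × 16 − 2 = 30 degrees of freedom. Power is the chance that a noncentral t variable exceeds the critical value: 2.042 at one-sided 0.025, 1.697 at one-sided 0.05.

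**Reproducing the plan's figure.** With d = 2.2:
- One-sided 0.05: 16 evaluable per group are needed for 90%. 16/0.75 = 21.3, rounded up to 22 per group, 44 in total. This matches the plan exactly.
- One-sided 0.025: 20 evaluable per group are needed. 20/0.75 = 26.7, rounded up to 27 per group, 54 in total. The normal approximation gives 18 evaluable, 24 per group and 48 in total. Neither is 44.
- With d = 0, 90% power needs 151 evaluable per group (one-sided 0.05) or 186 (one-sided 0.025). After dropout these are 202 and 248 per group, or 404 and 496 in total.

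So 44 arises from the 2.2-day advantage together with one-sided 0.05.

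**Power of the planned trial, 16 evaluable per group**

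| True FSN advantage (days) | Noncentrality | One-sided 0.025 | One-sided 0.05 |
|---|---|---|---|
| 2.2 | 3.2/1.047 = 3.06 | 84% | 91% |
| 1.1 | 2.1/1.047 = 2.01 | 49% | 62% |
| 0 | 1/1.047 = 0.96 | 15% | 24% |

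For 90% power with 16 per group, the true advantage must be about 2.5 days at one-sided 0.025 or about 2.1 days at one-sided 0.05.

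**Sensitivity**
- Taking 17 evaluable per group: 86% at 2.2 days and 16% at 0 (one-sided 0.025).
- No dropout at all (22 per group): 94% at 2.2 days at one-sided 0.025, but still 19% (0.025) or 29% (0.05) at equal efficacy.
- At equal efficacy with 16 per group, if both SDs were 2.3: 22% (0.025) and 33% (0.05). If both were 3.5: 12% and 20%.
- A Welch version changes these results by less than half a percentage point.

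**A superiority test at the same size.** Noncentrality 2.2/1.047 = 2.10. Power at two-sided 0.05 is about 53%, even if the 2.2 days is true.

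**The case against.** Assuming a favourable true difference is an accepted input to a non-inferiority calculation, and wanting to show that FSN is at least not inferior is compatible with expecting it to be better. The assumption is also open: section 2.4 prints both means and SDs, names an acupuncture trial as the source and admits the gap in FSN evidence. Every power figure is conditional on its inputs. The study is called exploratory, and section 7 lists the small sample as a limitation. Power tables for other effects and fallback wording for an inconclusive result are often left to a fuller document.

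Most of this stands, and it rules out some stronger readings that a reader might infer:

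- *The calculation is invalid because it assumes superiority.* It is not; the input is permissible.
- *The protocol hides the assumption or misleads about it.* The figures from which the 2.2 days follows are printed.
- *The real power is 15%.* That is the power in one scenario, equal efficacy, and the documents do not show that this is the true state.
- *The investigators would report a failed test as inferiority.* Nothing in the article says so; it is only a risk of interpretation.

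The objection does not rescue the 90% itself. The protocol puts that number beside a two-sided alpha of 0.05 and 25% dropout, and those inputs do not produce it. The word exploratory does not withdraw a numerical power claim for a formal test.

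**Conclusion.** The point holds in a limited form. On the protocol's own margin, SDs and dropout, 44 participants give about 84% power at the stated alpha, not 90%, if the borrowed 2.2-day advantage is true. Power falls to 49% at half that advantage and to 15% at none. At one-sided 0.05, the only level tried that reproduces 44, the figures are 91%, 62% and 24%.

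These results assume 16 evaluable per group, the reference trial's SDs and a t-based analysis. The shortfall from 90% to 84% also depends on the planned dropout occurring, since with everyone evaluable power at 2.2 days would be 94%. The steep loss of power at smaller advantages does not depend on dropout or on the choice of alpha. What is at fault is the stated power figure and its missing condition. The decision to assume a favourable effect is not.

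**What to change.** Keep 44 participants and amend the wording:

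1. In section 2.4, settle the alpha for the non-inferiority test first, then restate the power at that level. If two-sided 0.05 stands, give about 84% for a true FSN advantage of 2.2 days, 49% for 1.1 days and 15% for equal efficacy, with 16 evaluable per group. If one-sided 0.05 is what was meant, say so and give 91%, 62% and 24%.
2. In the same place, say that the headline figure is conditional on FSN being superior by the amount seen for another acupuncture technique.
3. Base the primary conclusion on the confidence interval for the between-group difference in MMD change, set against the 1-day margin. State that failure to exclude the margin will be reported as inconclusive, with the interval, and not as inferiority.

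A superiority test after non-inferiority is shown is optional. Section 6 already plans a two-sided comparison, and its power is only about 53% at 2.2 days.

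The cost is a few sentences in sections 2.4 and 6 and a less favourable stated power. No extra participants are needed.

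### The 1-day non-inferiority margin rests on common usage, not on flunarizine's controlled effect, so meeting it does not by itself show that FSN is efficacious

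*Protocol article*

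**What the plan says.** Section 2.4 (Sample size calculation) plans a non-inferiority test of FSN against flunarizine on the 4-week reduction in monthly migraine days (MMD). The margin is supported by one statement, with a citation: "the most commonly selected non-inferiority margin for Monthly Migraine Days (MMD) in migraine studies is 1".

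The planning figures come from an earlier acupuncture trial. There "the MMD in the acupuncture group decreased by 4.1 ± 3.5 from baseline" and "the MMD in the flunarizine hydrochloride group decreased by 1.9 ± 2.3 from baseline". Both are changes within an arm. The plan carries them over: "The hypothesis posited comparable effect sizes between the two interventions (FSN group and flunarizine hydrochloride group) in this trial and those observed". With a two-sided alpha of 0.05, 90% power and "an anticipated 25%dropout rate", it concludes that "a total of 44 participants (22 per group, 1:1 ratio) are required".

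Sections 2.2 and 2.5 describe two arms, FSN and flunarizine, and state that participants and practitioners are not blinded. Section 6 plans between-group tests of the change at two-sided p < 0.05 and does not refer to the margin. Section 8 restates the non-inferiority hypothesis and adds: "The results may demonstrate the clinical utility of FSN therapy for migraine without aura and facilitate its wider implementation".

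**The concern.** With only an active comparator, a non-inferiority result says something about efficacy only through a chain. The comparator must have a known effect over no active treatment, that effect must be present in this trial, and the margin must be smaller than it. Frequent use of a margin in migraine studies does not establish this for flunarizine at 4 weeks.

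The 1.9-day figure does not fill the gap. It mixes drug effect with natural course, expectation and regression to the mean. The last is plausible because section 2.3.1 requires at least two attacks a month and a VAS score above 3 at entry. The drug-specific part is not given. If it were 1 day or less, a treatment with no effect of its own would lie within the margin. No arm in this trial would reveal that.

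What is at stake is the meaning of the primary result. A statement of non-inferiority could be read as support for the clinical utility and wider use that section 8 anticipates, when it supports something narrower.

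**Working it through.** **Inputs, all from section 2.4.** Margin 1 day. Mean reductions 4.1 (SD 3.5) and 1.9 (SD 2.3), so the assumed FSN advantage is 4.1 − 1.9 = 2.2 days. Power 0.90, dropout 25%, 22 per arm. Flunarizine's net effect over no active treatment, δ, is not in the documents, so the values used below are assumptions.

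**1. The plan's own number.** The standard error of the difference is SE = √((3.5² + 2.3²)/n) = √(17.54/n). The distance from the assumed truth to the margin is 2.2 + 1 = 3.2 days.

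- Noncentral t, one-sided 0.05: 16 evaluable per arm (power 91%). 16/0.75 = 21.3, so 22 per arm and 44 in total. This matches the plan and confirms that the 1-day margin drives the sample size.
- One-sided 0.025, which corresponds to the stated two-sided 0.05: 18 per arm by the normal approximation (24 after dropout, 48 in total) or 20 by noncentral t (27 after dropout, 54 in total). That mismatch is a separate matter. The steps below use one-sided 0.025.

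**2. Margin against the only flunarizine figure.** 1/1.9 = 52.6%, or 53%. At the margin, FSN would show a reduction of 1.9 − 1 = 0.9 day, which is 47% of flunarizine's.

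**3. Margin against an assumed net effect δ.**

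| Assumed δ (days) | Margin/δ |
|---|---|
| 1.9 (whole change is drug effect) | 53% |
| 1.5 | 67% |
| 1.0 | 100% |
| 0.5 | 200% |

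The margin gives up the whole drug effect once the drug-specific share of the 1.9 days is about 53% or less.

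**4. How often an inert FSN would pass.** Here inert means no effect beyond what an untreated patient would show, so the true difference is δ in flunarizine's favour. Non-inferiority is declared when (observed FSN advantage + 1)/SE exceeds the t critical value, so the noncentrality is (1 − δ)/SE. SE is √(17.54/16) = 1.047 with 16 evaluable per arm and √(17.54/22) = 0.893 with 22.

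| Assumed δ (days) | 16 per arm | 22 per arm |
|---|---|---|
| 0 | 15% | 19% |
| 0.5 | 6.7% | 7.9% |
| 1.0 | 2.5% | 2.5% |
| 1.5 | 0.8% | 0.6% |

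The rates are low because the trial is small. With 16 per arm the critical distance is 2.042 × 1.047 = 2.14 days, so FSN must be observed ahead by about 2.14 − 1 = 1.14 days. With 22 per arm it is 2.018 × 0.893 = 1.80, so about 0.80 day. These rates assume no bias from the open design. Expectation favouring FSN would raise them by an amount the documents do not allow one to state.

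**5. Cost of a tighter margin.** Noncentral t with Welch degrees of freedom, distance 2.2 + margin.

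| Margin (days) | Power, 16 per arm | Power, 22 per arm (no dropout) | Evaluable per arm for 90% | Randomised with 25% dropout |
|---|---|---|---|---|
| 1.0 | 84% | 94% | 20 | 54 |
| 0.75 | 77% | 90% | 23 | 62 |
| 0.5 | 70% | 84% | 27 | 72 |

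Under the planned dropout, a smaller margin costs either power or patients.

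**The case against.** The strongest reply has four parts.

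- **The source may say more.** The article cites a source for the margin that cannot be seen here, and a full protocol may hold a fuller rationale. That is possible. But the article states a reason, and the reason as stated is about frequency of use.
- **The study is exploratory.** Sections 2.4 and 7 say so, section 7 calls for larger multicentre trials, and section 8 is hedged. This stands, and it lowers the severity. It does not remove the point, because the introduction and section 8 make non-inferiority the hypothesis and section 8 looks ahead to wider use.
- **Flunarizine is guideline-recommended.** That is a normal reason for an active comparator without placebo. It supports the choice of comparator. It does not say how large the drug's 4-week effect is, which is what the margin needs. The lack of a placebo arm is a design choice and is not criticised as such.
- **A false pass is unlikely.** Step 4 supports this for net effects of 0.5 day or more.

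Two stronger readings are tempting, and neither is supported. A reader might infer that meeting the margin can never show that FSN works. The documents give no net flunarizine effect. Outside evidence of a controlled 4-week effect reliably above 1 day would make a pass indirect evidence of efficacy, and a result showing FSN better than flunarizine would be a different finding. A reader might also infer that a tighter margin costs nothing because the plan assumes a 2.2-day advantage. Step 5 shows otherwise: with 16 evaluable per arm, power falls from 84% to 77% or 70%.

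**Conclusion.** The point holds as a limit on interpretation. The 1-day margin is justified by convention alone, equals 53% of an uncontrolled change, and is linked to no controlled effect or preserved fraction. Nothing in the design shows that flunarizine worked in these patients. On the evidence given, meeting the margin supports the statement that FSN is not worse than flunarizine by more than 1 day. It does not by itself support efficacy or clinical utility.

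The practical risk is modest: about 7 to 8% at an assumed net effect of 0.5 day, 2.5% at 1 day, and 15 to 19% in the extreme case of no net effect. These figures rest on the plan's SDs, a one-sided 0.025 test and no open-label bias. The documents do not show that 1 day is the wrong margin, only that its basis is not given. This is a should-fix, not a must-fix.

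**What to change.** - **Section 2.4:** describe 1 day as a clinical tolerance for being worse than flunarizine, unless a placebo-controlled flunarizine effect on 4-week MMD is cited to support it as an effect-preserving margin.
- **Section 6:** report the between-group difference in MMD change with its two-sided 95% confidence interval, and judge non-inferiority by whether that interval excludes a 1-day disadvantage for FSN.
- **Section 8:** state that meeting the margin supports only that FSN is not worse than flunarizine by more than 1 day. Reserve a claim of benefit over flunarizine for an interval that excludes zero in favour of FSN.

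The cost is a few sentences and a more modest conclusion. This point asks for no change to the 44 participants. Deriving a smaller margin is not requested, because it needs a figure the documents lack and would cost power or patients as in step 5.

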## Statistical analysis

6

Statistical analyses are conducted using SPSS 25. All tests employ two-sided comparisons, with statistical significance defined as *p* < 0.05.

Normally distributed continuous variables are presented as mean ± standard deviation (SD), whereas non-normally distributed variables are reported as median and inter-quartile range (IQR). Categorical variables appear as frequency and percentage (proportions).

For the MMD, MSQOL, MIDAS and VAS scale scores, between-group differences in changes from baseline to 4 weeks post-treatment are analyzed using either the independent *t*-test or Mann–Whitney U test, as appropriate. Intra-group comparisons between baseline and 4-week post-treatment measurements are conducted using paired *t*-test or Wilcoxon signed-rank test. Given the repeated measurements of MMD and the scale scores, repeated-measures analysis of variance (ANOVA) is additionally employed for supplementary analysis. For near-infrared spectroscopy (NIRS)-derived oxygen saturation levels, analyzed for within-group differences before and after treatment using paired *t*-test.

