This study has several limitations. This study is a single-center trial with a small sample size (*n* = 60), which may be subject to selection bias, thereby limiting the generalizability of its findings to different populations or settings. Due to the inherent characteristics of acupuncture and pharmacotherapy, blinding both practitioners and participants presents considerable challenges, potentially increasing the risk of bias. To mitigate this risk, the intervention operators, outcome assessors, data collectors, and statisticians are all independent researchers. All personnel, except the operators, remained blind to group allocation. Standardized operating procedures are implemented to ensure adherence to treatment and assessment protocols, thereby minimizing unintended influences on outcome measures. The use of rescue medications may interfere with the evaluation of headache intensity and frequency; therefore, the final analysis will comprehensively document and compare intergroup medication usage (dosage, frequency, time to onset). Subsequent studies should establish unified guidelines. Limited by current equipment, near-infrared spectroscopy monitoring focused solely on hemodynamic changes in the prefrontal cortex and did not assess the effects of FSN on other brain regions. As an exploratory study, this trial aimed to investigate whether FSN may reduce patients’ reliance on flunarizine, decrease drug-related side effects, and provide a safe alternative for patients with contraindications to medication. Future large-scale, multi-center clinical trials are warranted to validate the long-term efficacy of FSN and its potential as an adjuvant or first-line treatment.

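### The sample size of 44 does not match the stated two-sided alpha of 0.05: after the planned 25% dropout, power is about 84%, not 90%; the Discussion also gives n = 60

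*Protocol article*

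**What the plan says.** Section 2.4 of the protocol article gives every input to its calculation. The expected changes come from a reference acupuncture trial: "the MMD in the acupuncture group decreased by 4.1 ± 3.5 from baseline" and "the MMD in the flunarizine hydrochloride group decreased by 1.9 ± 2.3 from baseline". The section carries these over to the present trial: "The hypothesis posited comparable effect sizes between the two interventions" here and those in the reference trial. The non-inferiority margin is 1 monthly migraine day, and the procedure is a PASS 15.0 non-inferiority test for two means. Alpha is given as "0.05 (two-sided), power" is set at "0.9, and an anticipated 25%dropout rate", and the result is 22 per group, 44 in total: "and an anticipated 25%dropout rate, a total of 44 participants (22 per group, 1:1 ratio) are required".

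Section 6 applies the same error rate to the analysis: "All tests employ two-sided comparisons, with statistical significance defined as" p below 0.05.

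The abstract and sections 2.2 and 2.5 agree with 44 in total or 22 per group, and section 2.5 describes 44 envelopes. The limitations paragraph of section 7 instead refers to a "small sample size (*n* = 60").

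**The concern.** A non-inferiority test rejects in one direction only. A two-sided alpha of 0.05 therefore means testing at one-sided 0.025, equivalently reading the lower limit of a 95% confidence interval against the margin. A sample size worked out at one-sided 0.05 is smaller. If 44 belongs to the looser error rate while the article states and analyses at the stricter one, the trial does not have its stated 90% power under its own dropout assumption. Readers would then misjudge the chance of a false negative on the primary question. The figure of 60 adds doubt about which size is planned.

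**Working it through.** **Inputs, all from section 2.4.** Mean reductions 4.1 (SD 3.5) and 1.9 (SD 2.3), so the assumed difference is 4.1 − 1.9 = 2.2 days in favour of FSN. Margin 1, so the distance from the assumed difference to the margin is 2.2 + 1 = 3.2. Sum of variances: 3.5² + 2.3² = 12.25 + 5.29 = 17.54. Power 0.90, dropout 25%, allocation 1:1.

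**Formula.** With n evaluable per group, the standard error is √(17.54/n) and the noncentrality is 3.2/√(17.54/n). Power is the probability that a noncentral t with 2n − 2 degrees of freedom exceeds the one-sided critical value. Enrolment per group is n/(1 − 0.25), rounded up.

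**Step 1: reproduce 44.** At one-sided 0.05:
- n = 15 gives power 0.893, too low.
- n = 16 has noncentrality 3.2/√(17.54/16) = 3.2/1.047 = 3.06 and gives power 0.910.
- 16/0.75 = 21.3, rounded up to 22 per group, so 44 in total. This is an exact match.

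**Step 2: repeat at the stated alpha.** Two-sided 0.05, that is one-sided 0.025:
- n = 19 gives 0.8998, just short of 0.90.
- n = 20 has noncentrality 3.2/√(17.54/20) = 3.2/0.936 = 3.42 and gives 0.915.
- 20/0.75 = 26.7, rounded up to 27 per group, so 54 in total. If 19 were accepted, 19/0.75 = 25.3, so 26 per group and 52 in total.

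**Step 3: check by normal approximation.** n = (z for alpha + z for power)² × 17.54/3.2².
- One-sided 0.025: (1.95996 + 1.28155)² × 17.54/10.24 = 17.998, so 18. Then 18/0.75 = 24 per group, 48 in total.
- One-sided 0.05: (1.64485 + 1.28155)² × 17.54/10.24 = 14.67, so 15. Then 15/0.75 = 20 per group, 40 in total.

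Neither gives 44.

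**Step 4: power of the design as planned.** 22 × 0.75 = 16.5 evaluable per group. At one-sided 0.025:

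| Evaluable per group | Power (t) | Power (normal approximation) |
|---|---|---|
| 16 | 0.841 (0.837 with unequal-variance degrees of freedom) | 0.864 |
| 17 | 0.863 | 0.883 |
| 22 (no dropout) | 0.938 | 0.948 |

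After the planned dropout, power is below 0.90 by either method.

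**Step 5: the figure of 60.** The abstract and sections 2.2, 2.4 and 2.5 all give 44 or 22 per group. The 60 appears once, in the limitations paragraph of section 7, with no derivation.

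**The case against.** Several points on the other side are fair.

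- **The shortfall depends on dropout.** With all 22 per group evaluable, power is about 94%; with 19, a loss of 3/22 or about 14%, it is still about 90%. This stands as a condition, so 84% must not be quoted as the trial's power without it. It does not rescue the text, because the 90% is claimed after allowing for 25% dropout.
- **One-sided 0.05 is not the only route to a number near 44.** At one-sided 0.025, the normal approximation gives 18, and the incorrect inflation 18 × 1.25 gives 22.5 per group. That route needs an approximation, a wrong dropout formula and rounding down, and it still leaves power below 90% after 25% loss. The cause therefore remains open. A reader might infer that 0.05 was typed into a one-sided software field, but the article names only the PASS procedure and shows none of its settings.
- **The required total depends on method.** It is 54 by the t calculation and 48 by the normal approximation. Both exceed 44.
- **Assuming FSN to be better is legitimate.** A reader might infer that the 2.2-day advantage is concealed, or that it contradicts a hypothesis of non-inferiority. Neither holds: section 2.4 prints both means and says the reference trial's effects are carried over, and a non-inferiority trial may be powered on an expected advantage. Power under equal effects would be a useful sensitivity figure, but its absence is not an error.
- **The study is called exploratory.** That lowers the stakes, but section 2.4 still makes a formal power claim that its own inputs do not support.

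**Conclusion.** The point holds: the alpha, power, dropout and sample size in section 2.4 cannot all be right together. On the stated inputs, 44 corresponds exactly to one-sided 0.05 with 91% power at 16 evaluable per group. At the stated two-sided 0.05, power after 25% dropout is about 84% (86% with 17 evaluable per group), so the chance of missing non-inferiority is about 16% rather than 10%. These figures assume a true 2.2-day advantage for FSN, the quoted SDs and a t-based test against the 1-day margin. Section 6 confirms the two-sided level, so nothing elsewhere in the article resolves the mismatch. The n = 60 is a separate, isolated inconsistency in the Discussion. It does not put the planned size in doubt, since every operational statement gives 44.

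**What to change.** Keep 44. In section 2.4, state alpha as 0.05 two-sided (one-sided 0.025 for the non-inferiority test), and give power as about 84% after 25% dropout, with 16 evaluable per group, under the assumed 2.2-day advantage for FSN.

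If one-sided 0.05 was in fact intended, section 2.4 should say so and section 6 must change with it, with non-inferiority judged on a 90% confidence interval. Relabelling section 2.4 alone would leave the two sections in conflict.

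In the limitations paragraph of section 7, correct n = 60 to 44.

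The cost is text only, with no added participants; under the main option the stated power becomes less favourable. Retaining 90% power at two-sided 0.05 after 25% dropout would instead take 54 participants by the t calculation, 54 − 44 = 10 more.
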